#### **Demonstrate the patient-centeredness of the application (Criterion 4)**

By comparing the effectiveness and safety of two alternative approaches valued by patients to reduce harm from cigarette consumption, our research proposal fits squarely in the priority area: ‘Assessment of Prevention, Diagnosis, and Treatment Options’. It matches closely with 3 of the top 10 PCORI Comparative Effectiveness Research Priority areas: Prevention (preventing harm from smoking related diseases, e.g. lung cancer), Chronic Disease (reducing smoking related complications from chronic diseases (e.g. COPD), and Patient Engagement (building upon risk reduction approaches currently being used by many patients, but not widely promoted in the health care community). Our analytic methods will provide specific answers for patients with key PCORI-like questions such as:

- ‘Given my personal characteristics and preferences, what should I expect will happen to me if I try to quit right away versus start long term nicotine replacement?’;
- ‘Is long-term nicotine replacement a realistic option for me?’;
- ‘What are the potential benefits and harms of long-term nicotine replacement versus trying to quit right away?’; and
- ‘What can I do to improve the outcomes that are most important to me, such as reducing my smoking, reducing my exposure to cancer-causing toxins, and ultimately being able to quit smoking long term?’

Our research specifically addresses current gaps in knowledge related to the role of long-term NRT in reducing harms of cigarette smoke. The findings have the potential to influence decision-making of key stakeholders related to smoking cessation guidelines and reimbursement for smoking cessation treatment. Our study is inclusive of different populations in both the planning and implementation of the research, by including low-income smokers, African Americans, and Latinos. Finally, the development and implementation of the study are highly patient centered, addressing research questions posed by smokers and outcomes valued by smokers with COPD.

We utilized a variety of approaches to ensure the engagement of patient's and stakeholders in the design and conduct of the proposed research project. We reviewed the literature to identify patient-centered research studies that captured the perceived needs and interests of smokers and patients with COPD. We reviewed guidelines and consensus statements in order to capture the perceptions of key stakeholders. We spoke directly with smokers with COPD that have been grappling with issues related to smoking cessation and harm reduction. We conducted semi-structured interviews with these smokers, soliciting their perceptions on critical components related to the design and conduct of the proposed study. We also convened a Patient Advisory Panel that has provided critical input into this proposal and will continue to guide the investigators throughout the conduct of the study. Finally, we used the support of the Tobacco Free Kansas Coalition to bring together key stakeholders, including health care providers, public health experts, and representatives of key stakeholder organizations. Each of these approaches is delineated below.

Our research addresses issues raised by patients and stakeholders as illustrated by a national survey of 1,000 smokers. Of these smokers, 29% had no interest in changing their smoking habits over the ensuing year, but the other 71% varied substantially in how they wanted to address smoking cessation or harm reduction. While one in four were interested in the traditional approach to smoking cessation; the other 3/4ths wanted to either cut back on smoking but not quit completely (harm reduction) or, more commonly, gradually reduce their smoking as a prelude to quitting. The majority of these smokers were interested in using nicotine replacement to help them reduce the number of cigarettes that they smoke with slightly more preferring patch than gum. These findings were corroborated by the ITC Four Country Survey which showed that many smokers are already using NRT for reasons other than quitting. In light of these findings, it is not surprising that current cessation programs are failing to reach the majority of smokers. Not surprisingly, the Consumer Demand Roundtable of the National Tobacco Cessation Collaborative concluded that current clinician-oriented cessation programs are only reaching a small portion of the patients in need. They concluded that the needs, interests and perspectives of smokers needed to be heard in order to develop more effective strategies.

In recognition of this, we asked our patients to help us develop this research proposal, including the choice of the research question, the design of the intervention, and the outcomes included. We started by conducting structured interviews with 21 smokers with COPD. While only a minority of these smokers (7), were ready to try to quit within the next 30 days, almost all were interested in cutting down, primarily to improve their health, improve their breathing, and reduce their risk of cancer (outcomes that we have incorporated into this study). Some expressed concerns about the safety of Chantix. Most (18) were very interested in the idea of using NRT long term to either help them quit or simply to reduce their exposure to the harm from cigarettes, and the majority were interested in participating in a study that would help them reduce their smoking, even if they had to take medications long term.

We invited five smokers with COPD to serve on a 'Patient Advisory Panel' to tell us about the issues that were most relevant to them, to help us interpret the results of our literature review and structured interviews, and to guide us in choices related to research questions, study design, and relevant outcomes. The Panel reinforced the findings of the structured interviews related to important outcomes. They voiced strong support for an intervention that would allow them to quit gradually, and they were very interested in using NRT prior to quitting, using NRT instead of Zyban or Chantix, and using combination NRT. They warned us that very few patients will have tried combination therapy with NRT, so this will have to be addressed in our patient education, but they thought the idea of using combination therapy would be very appealing to many smokers. They also warned us of the need to create clear 'troubleshooting procedures' for the NRT and recommended that we provide choices of gum versus lozenge and offer different choices of flavors.

Although patient engagement was critical to the design of this study, we recognize that implementation of research findings will be critically dependent upon the support of other stakeholders, including health care providers, public health experts, and the community organizations that have been at the forefront of the fight against tobacco. Drs. [name] and [name] have worked extensively with the Tobacco Free Kansas Coalition (TFKC) – a coalition of community organizers, private voluntary organizations, health care providers, and public health representatives. Drs. [name] and [name] continue to serve on the cessation committee of the TFKC, and [name] currently serves on the board of directors. On behalf of the TFKC, Drs. [name] and [name] personally testified at local and state-level government hearings across Kansas in support of clean indoor air laws; they continue to support the organization with scientific guidance and testimony on tobacco related issues. In support of this project, the TFKC helped the researchers identify stakeholders to serve on the Stakeholder Advisory Committee who, in turn, are advising us on the design and conduct of this study. This committee includes [name], Executive Director, TFKC; [name], primary care physician and TFKC board member; [name], primary care physician and former TFKC board member; [name], Kansas state quitline coordinator, [name], public health practitioner and advocate; [name]; epidemiologist/toxicology expert; [name], American Cancer Society; [name], American Heart Association; and [name], American Lung Association. (see attached letters of support) This subcommittee reviewed this proposal and provided critical input into the study design, including issues related to participant inclusion, outcome measurements, and treatment. The health care professionals on this committee shared with us their frustration with the current treatment options for patients with COPD that smoke; they were particularly enthusiastic about the potential of initiating long term NRT to reduce smoke exposure and enhance the potential of ultimately quitting.

## **Demonstrate the commitment to patient and stakeholder engagement (Criterion 5)**

**Prior history of patient and stakeholder engagement.** [name] is a practicing physician who engages with smokers and patients with COPD on a regular basis in his clinical practice. He and his team of co-investigators are deeply indebted to the health care providers and smokers throughout Kansas that have played a critical role in their past work. He and [name] visited more than 50 clinics and hospitals around the state of Kansas to discuss smoking cessation and identify better ways to integrate smoking cessation into clinical practice. The insights gained from this work were critical to the successful implementation of the UKanQuit program at KUMC. The physicians in the Kansas Physicians Engaged in Prevention Research practice-based research network helped with the design and implementation of a chronic disease model for smoking cessation. Smokers throughout rural Kansas gave us insights into the culture of rural smoking, and showed us how this model could be adapted to address the needs of smokers in rural primary care. Smokers in drug treatment shared their experiences on cessation attempts and their strong interest in harm reduction, leading to a variety of efforts to try to improve tobacco control in the context of drug treatment. We built upon the lessons learned in these past efforts to engage patients and stakeholders for this project.

### **Patient and Stakeholder engagement to date for this project:**

As described in the previous section, we have already engaged patients and stakeholders in the design of this research project and the formulation of the research questions, conducting structured interviews with smokers, convening a Patient Advisory Panel and meeting with our Stakeholder Advisory Committee. The findings from this engagement are described under Criterion 4 and incorporated throughout the actual design of the study (Criterion 3).

### **Plan for ongoing patient and stakeholder engagement:**

At the heart of our ongoing engagement plan is our Patient Advisory Panel. We have already engaged a preliminary group of panel members, but will recruit additional panel members to enhance representation of our multicultural patient population. Our Patient Advisory Panel will include patients with COPD, some who have quit and some who continue to smoke. Our final panel will consist of approximately 8 members representing the full diversity of our COPD population. We will engage our stakeholders and local health care providers to help us identify potential panel participants. We will convene our panel members immediately

upon notice of award so that they can review the study design, recruitment methods, interventions, and outcomes assessments. Meetings will be conducted at convenient times with free parking and easy access. (Some panel members will be using oxygen.) We will provide a \$75 stipend to cover their time and the cost of transportation for each meeting. Panel members will convene semi-annually, but our initial panel expressed a willingness to use telephone and e-mail on an as-needed basis between meetings. We will do our best to incorporate input from Panel members into the study so long as it does not compromise the technical merit of the research design. We plan to hold one meeting each year in conjunction with the Stakeholder Advisory Committee (see below). At each meeting panel members will receive project updates and we will solicit their input on project-related activities such as participant recruitment, data analysis, and interpretation of study findings. Meetings of the Patient Advisory Panel will be led by [name], a psychologist with substantial experience in engaging participants in open discussion.

Our Stakeholder Advisory Committee (described under Criterion 4) will continue to work on the planning and implementation of this study. The Committee convened immediately upon notice of study award to provide input into any modifications needed in the study design, recruitment methods, interventions, or outcome assessments. This initial meeting was particularly important in verifying that our study can lead to results that would be actionable by the stakeholders. Committee members will reconvene twice a year, once by conference call and once face-to-face, in conjunction with our Patient Advisory Panel. At these semi-annual meetings, committee members will advise the investigators on a variety of issues including participant recruitment, data analysis, publication, and dissemination of results. Committee members also expressed a willingness to meet by phone or e-mail on an as-needed basis.

***Taking advantage of patients and stakeholders to help disseminate actionable findings***

Both our Patient Advisory Panel and our Stakeholders will be highly engaged in our analysis plans and dissemination of results. We will work with both Panel members and Stakeholders to identify opportunities for joint presentations, publications, or media events. Panel members, in particular, will be important in formulating press releases and speaking to the media. Both Panel members and Stakeholders will be prepared for these presentations and events since they will have been engaged in planning the analysis (particularly the CART model and decision tree). Prior to publication and dissemination of findings, the Stakeholder Advisory Committee will review scientific reports and drafts of publications to ensure that the messages included in these reports are relevant to clinicians and policy makers. In year 3 of the project, we will have a combined meeting of the Patient Advisory Panel and the Stakeholder Advisory Committee to review findings in lay language, assuring that the dissemination of the findings reflects the underlying scientific findings, but can also be easily understood by the community at large. Both groups will help us incorporate findings into our website and disseminate findings to the public (e.g. press releases). Furthermore, panel members will help design our study website. In addition to highlighting study findings and protocols, the website will allow interested patient advisors or study participants to share personal stories of their experiences of quitting smoking, smoking with COPD, etc. We will also work closely with our Stakeholder Advisory Committee to get study findings into the hands of guideline developers and key national stakeholders.

Working jointly with our Patient Advisory Panel and our Stakeholder Advisory Committee, we will take advantage of our connections with national organizations and smoking cessation experts to disseminate results. As president of AMERSA (Association for Medical Education and Research on Substance Abuse), [name] has ready access to some of the nation's leading experts on nicotine addiction and smoking cessation. We will take advantage of listserves established by AMERSA and SRNT (the Society for Research on Nicotine and Tobacco) to discuss findings with other researchers. We will also use meetings of the Society for Research on Nicotine and Tobacco, the Society for Behavioral Medicine, and the Society for General Internal Medicine as opportunities for networking and dissemination.

## DISSEMINATION AND IMPLEMENTATION POTENTIAL

Our study and analytic plan are well designed to produce results that are amenable to widespread dissemination and rapid implementation. Dissemination will occur through presentations at national meetings, publications in the peer-reviewed literature, distribution of study findings in the lay media, development of a study website, and adoption of study findings in clinical practice guidelines and by advocacy groups. To enhance implementation of the study findings, the patient-centered decision tree (Aim 2) will be posted on the web and can be incorporated into electronic health records. Perhaps the most critical aspect of implementation, however, will be the use of these study findings to advocate for policy changes in coverage of NRT by insurance plans.

We will subject study findings to peer review at national meetings and in the peer-reviewed literature. Drs. [name], [name], and [name] plan to present the findings of this study at a variety of national meetings such as the Society for Research on Nicotine and Tobacco, the Society for Behavioral Medicine, and the Society of General Internal Medicine. Findings will also be published in the peer reviewed-literature. Publication is critical to procuring the attention of advocacy groups and guideline developers. Along with publication and presentation of our findings, we will take advantage of the KUMC media department to prepare press releases related to our study. We have a strong track record in procuring regional and national coverage of our research. (We plan to make extensive use of our Patient Advisory Panel and our Stakeholders in this part of the dissemination process.) We will also work with PCORI staff to support dissemination on their website, listserv, and other distribution channels.

Our Stakeholder Advisory Committee includes representatives of some of the most prominent national and regional advocacy groups concerned with smoking related illnesses. We will work with both the regional and national offices of these stakeholders to identify channels of distribution of the study findings and identify ways to get the study findings incorporated into their organizational guideline development programs.

The most prominent guideline related to tobacco control policy is the guideline produced by the US Preventive Services Taskforce. Our investigators know many of the authors of these guidelines personally and interact with them at national meetings, in particular through the Society for Research on Nicotine and Tobacco. We will work with these guideline developers to see if the findings of our study can be incorporated into the next update of these guidelines. Incorporation of study findings into clinical practice guidelines can have tremendous implications for driving policy changes that can drive implementation of these findings.

Dissemination to patients, stakeholders (particularly clinicians), and policymakers, as outlined above, are critical to implementation, but implementation will also be facilitated by the publication of our 'decision tree' which will help patients and clinicians understand the relative merits of treatment choices given the smokers unique characteristics (Aim 2). This decision tree will be published on the web and made accessible world-wide. We propose to incorporate the decision tree into our own EPIC electronic health record at KUMC and share this adaptation to the EPIC learning community. EPIC is the most widely used electronic health record in the United States and EPIC users have a variety of tools available for sharing innovations across institutions, including an EPIC users group associated with the NIH's Clinical and Translational Research Centers program of which KUMC is a member. As the decision tree gains acceptance, it can be distributed across other electronic health record platforms.

Perhaps the most important step in the implementation of study findings will be related to making changes in insurance coverage for NRT. Insurance coverage for NRT varies substantially across health plans, but in general, insurance companies have placed limits on the duration of NRT use and do not cover combination therapy. [name] has been directly involved in working with state Medicaid programs on revising coverage of services for smoking cessation. Given specific provisions within the affordable care act, making these changes in coverage decisions will be much easier if the findings of this study are incorporated into

clinical practice guidelines – as noted above.

**Describe possible barriers to dissemination and implementation of your work in other settings.**

There will be several potential barriers to dissemination and implementation of our study findings. Perhaps the biggest barrier will be the entrenched attitude in both the practitioner and lay community that smoking is a 'personal choice' and therefore smoking cessation services shouldn't be covered under insurance policies. Indeed, there has been a long history of insurance companies and employment benefit plans excluding treatment coverage for 'lifestyle choices' such as smoking cessation. We believe that new understanding of the neurophysiology of nicotine addiction is changing these attitudes, but the attitudes persist nonetheless.

The next biggest barrier will be getting the actual changes made in the guidelines. Guideline development takes time and requires negotiation among many individuals with varying interests and backgrounds. Our study, however, directly addresses many of the research priorities delineated in the most recent iteration of the guidelines and the technical rigor of our study design and analytic plan should facilitate incorporation of findings into future guidelines.

Finally, getting clinicians to actually incorporate research discoveries into clinical practice has long been a challenge. Indeed, our research team has already demonstrated the difficulties that many primary care practitioners have in incorporating existing guidelines into their practice. We have, however, been at the forefront of efforts to integrate tobacco treatment services into electronic health records and we believe that integration into electronic health records, along with performance monitoring could, at least in part, address this concern.

## REPRODUCIBILITY AND TRANSPARENCY OF RESEARCH

While the findings generated from this proposed research have direct relevance to the 5 million Americans with COPD that smoke, this study could be easily replicated in other populations with implications for the 43 million smokers in the United States. Our protocol, intervention materials, and counseling procedures will be freely available to facilitate implementation of our study findings into clinical practice or replication of our study in other populations. Our study will include a diverse population of smokers representing low-income patients, whites, African Americans, and Latinos. Our CART analysis will allow us to test for differential effects based on ethnicity, but this analysis would not preclude efforts to replicate this study among Latino or African American smokers, who have been noted to have lower rates of smoking cessation than white smokers. The protocol could also be readily adapted for use in the American Indian population which has particularly high rates of smoking and low rates of success with traditional cessation efforts.

Findings could also be replicated in other clinical populations, including populations with other chronic diseases such as heart disease, diabetes, substance abuse disorders, or isolated nicotine dependence. Larger sample sizes, however, might be required to identify changes in clinical outcomes in these populations since rates of clinical events would be expected to be much lower.

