### **Matching patients with optimal treatment based on their own characteristics**

Our classification and regression tree (CART) analysis will allow us to provide more personalized recommendations for smokers with COPD and facilitate dissemination. CART is an analytical approach used as an alternative to logistic regression for the identification of subgroups of individuals who may have differential response to treatment. It can be used to develop a decision tree to guide clinical decision making. CART uses statistical methods to cluster individuals into different groups that have different outcomes related to the treatment. Using CART, multiple individual characteristics (e.g., gender, cigarettes

per day (cpd), cotinine level, readiness to quit, treatment assignment, etc.) can be considered simultaneously and variables can be identified that efficiently separate individuals into groups that are more or less likely to experience a positive outcome (e.g., abstinence). These variables can then be incorporated into a decision tree that will show the predicted outcome (response to treatment) based on a patient's given characteristics. The total number of splits or branches in the resulting decision tree depends on the number of critical variables identified in the CART analysis. The complexity of the decision tree can adapt itself to the complexity of the data. As a nonparametric approach, CART does not require specification of the nature of the relationship between predictors and outcome or a priori assumptions about the true model.

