**Specific Aim 2: Develop estimates of patient-desired outcomes based on patient-specific characteristics and treatment choice (SSC vs. LT-NRT)** We will employ a Classification and Regression Tree (CART) analysis to identify subgroups of participants whose personal characteristics might impact the benefit of treatment. The resulting decision tree will allow smokers and their care providers to estimate their individual chances of success given their choice of treatment. To maximize the utility of the decision tree, we will start by soliciting input from our Stakeholder Advisory Committee and Patient Advisory Panel. We will ask them to identify key demographic, psychosocial, biological, and smoking factors from Table 5 and help us convert them into clinically meaningful binary variables that could be tested for inclusion in a clinically meaningful decision tree. (Drs [name] and [name] will provide both groups with simple conceptual models to assist them in providing meaningful, independent contributions.) The candidate variables, along with treatment assignment (LT-NRT vs SC) will be entered into a recursive partitioning model as described by Brieman and Friedman using the RPART package in the R statistical software. Specific methods related to building the tree (using appropriate splitting criteria and loss incorporation using the altered priors method), pruning the tree and handling missing data (using surrogate variables) will be deployed using the techniques described by Therneau et al. Given the event rates expected and overall sample size, a validation subsampling scheme will not be feasible, thus we will utilize 10-fold cross-validation on the regression tree to assess its properties. Additionally, we will account for the uncertainty in tree classification by generating a bootstrap sampling distribution of the CART as described by Shalizi. In addition to developing a CART model/decision tree for smoking cessation, separate classification models will be developed for other high priority binary outcomes, including: 1) 6 month sustained abstinence; 2) 50% reduction in carcinogen (NNAL) exposure; and 3) COPD related hospitalization (yes/no). (These were the models of greatest interest for our initial Patient Advisory Panel, but other outcomes could be modeled as well if our patients and stakeholders think that these additional models might be useful.)

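### The protocol names CART as the test for differential treatment effects by ethnicity, but a split in the planned tree shows that ethnicity predicts the outcome, not that the treatment effect differs

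*Protocol*

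**What the plan says.** Under Reproducibility and Transparency of Research, the protocol states that "Our CART analysis will allow us to test for differential effects based on ethnicity". The same sentence describes Latino and African American smokers as groups "who have been noted to have lower rates of smoking cessation than white smokers". The section on matching patients with treatment likewise presents CART as a tool for "identification of subgroups of individuals who may have differential response to treatment", although it goes on to describe the splits as separating people by how likely they are to have the outcome.

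The method is in the Analytical Plan, Specific Aim 2: "The candidate variables, along with treatment assignment (LT-NRT vs SC) will be entered into a recursive partitioning model". The tree is built "using appropriate splitting criteria and loss incorporation using the altered priors method". It is then pruned, and "we will utilize 10-fold cross-validation on the regression tree to assess its properties". A bootstrap distribution of the tree is added. No prior, loss or pruning value is given.

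Specific Aim 1 separately says that, if treatment differences turn out to be heterogeneous across covariate subgroups, the interactions will be quantified and reported with contrasts. Race and ethnicity are among the covariates in Table 5. The reproducibility section does not refer to that analysis.

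**The concern.** A differential effect by ethnicity means a treatment-by-ethnicity interaction, so the null hypothesis is that the treatment effect is the same in every group. The planned tree works against a different null. At each node it asks which variable best separates abstinent from non-abstinent participants, and cross-validation keeps a split that improves prediction. For ethnicity the relevant null is no association with abstinence, and the protocol itself reports that cessation rates differ between ethnic groups. The procedure can thus respond to a prognostic difference that is already believed to exist, while the text invites the reader to see a difference in response to treatment.

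This matters because the tree is meant for the web and for electronic health records. An ethnicity branch carrying the label of a tested differential effect could lead patients and clinicians to believe that one treatment suits one ethnic group less well, when the data show only different quit rates.

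**Working it through.** **1. The plan's own figure.** Inputs from Sample Size and Power Calculations: 10% in SSC, a two-fold rate (20%) in LT-NRT, 5% type I error (taken as two-sided), 80% power. With pooled variance and no continuity correction:

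n = [1.960·√(2·0.15·0.85) + 0.842·√(0.10·0.90 + 0.20·0.80)]² / 0.10² = 199 per arm.

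The stated size is reproduced. The matching odds ratio is (0.20/0.80)/(0.10/0.90) = 2.25. The protocol gives no figure for the CART analysis by ethnicity.

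**2. A case with no interaction.** Assume a 40% minority share and an ethnicity odds ratio of 0.5 for quitting. An SSC rate of 10% overall then requires 12.3% and 6.55%, since 0.6·12.3 + 0.4·6.55 = 10.0. Multiplying both odds by 2.25 gives 24.0% and 13.6% in LT-NRT. The treatment odds ratio is the same in both groups, yet pooled over arms the ethnic groups differ: (12.3 + 24.0)/2 = 18.1% against (6.55 + 13.6)/2 = 10.1%. That pooled gap is what an outcome tree can detect.

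**3. How often the tree splits on ethnicity.** Simulation with RPART: classification tree, default complexity 0.01, 10-fold cross-validation, n = 398, 400 trials per row, treatment odds ratio 2.25 in every group, no interaction. Assumed: altered priors 0.5/0.5, 40% minority share, and four binary noise candidates beside treatment and ethnicity. The second column is the normal-approximation power of a plain two-group comparison of ethnic groups at 15% overall abstinence.

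| Ethnicity OR | Power of plain ethnicity comparison | Split on ethnicity, minimum-CV pruning | Split on ethnicity, 1-SE pruning | Logistic interaction test rejects |
|---|---|---|---|---|
| 1 | 5% (nominal) | 25% | 9% | 5.5% |
| 0.7 | 22% | 35% | 20% | 4.8% |
| 0.5 | 62% | 57% | 40% | 3.5% |
| 0.33 | 94% | 89% | 80% | 3.2% |

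A repeat run at OR 0.5 gave 65% and 48%, hence the range of 40–65%. At OR 0.7 it gave 33% and 18%. The split rate rises with the prognostic strength of ethnicity, although there is no interaction in any row.

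Sensitivity to the assumptions:
- 20% minority share, OR 0.7 and 0.5: 32% and 52% (minimum CV); 17% and 33% (1-SE).
- Treatment and ethnicity as the only candidates, OR 0.7, 0.5 and 0.33: 22%, 60% and 87% (minimum CV); 15%, 49% and 77% (1-SE).
- No altered priors: at most 1.5% after pruning.

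**4. Trees that look like an interaction.** A narrower count takes only trees with exactly one treatment split and one ethnicity split. These show treatment mattering in one ethnic group only, or ethnicity mattering in one arm only. At OR 0.5 with no interaction they occurred in 32% (minimum CV) and 16% (1-SE) of trials, against 4% rejections by the interaction test.

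**5. Does a split separate the two situations?** With a real interaction (ratio of treatment odds ratios 0.5, no ethnicity effect in SSC), the tree split on ethnicity in 67% and 46% of trials. With a purely prognostic ethnicity OR of 0.5 and no interaction it did so in 57–65% and 40–48%. The presence of a split barely tells the two apart. The interaction test rejected in 18% and about 4% respectively.

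**6. What the interaction test can detect.** Holding 10% and 20% in both ethnic groups, Var(log ratio of ORs) = Σ 1/[199·share·p(1−p)] over the four cells. At a 40% share: 0.140 + 0.079 + 0.093 + 0.052 = 0.364, SE 0.603, and exp[(1.960 + 0.842)·0.603] = 5.4. At a 20% share: 0.279 + 0.157 + 0.070 + 0.039 = 0.545, SE 0.738, giving 7.9. At 50% it is 5.2. So 80% power needs a ratio of odds ratios of about 5 to 8.

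**The case against.** The best defence is that an interaction analysis already exists. Aim 1 promises to quantify and report interactions with contrasts, and ethnicity is a listed covariate. A reader might infer that the protocol plans no interaction analysis at all; that would be wrong. But the Aim 1 sentence applies only once heterogeneity has been found, does not say how it is found, and does not name ethnicity, while the reproducibility section still names CART as the test.

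A second defence is that the offending sentence is a caveat in a section on replication. This stands in part. A reader might infer that the tree's result is meant to guide replication in Latino and African American smokers. The protocol says only that the analysis would not stand in the way of such replication.

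Third, the candidate variables, loss values and pruning rule are details commonly left to a statistical analysis plan. That is fair, and their absence is not the point. The point is that the protocol affirmatively assigns a hypothesis to a method that does not test it. Pruning, cross-validation and the bootstrap address prediction and stability; none of them contrasts treatment effects between groups.

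**Conclusion.** The point holds as a misassigned test. An ethnicity split in the planned tree can arise when the treatment effect is the same in every group, and often does if ethnicity is strongly prognostic and altered priors are used.

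Two stronger readings are tempting and not supported. One is that the tree will usually split on ethnicity. That depends on the ethnicity effect, the priors and the pruning rule, none of which the protocol quantifies. Under the assumptions shown the rate runs from almost never (no altered priors) to 80–90% (OR 0.33), so no single rate can be fixed. The other is to count every ethnicity split as a false finding of interaction. A tree without a treatment branch says nothing about differential response. The narrower count of interaction-looking trees, about 16–32% at OR 0.5, is the fairer comparison with the nominal 5%.

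The same treatment effect here means the same odds ratio. With different baseline rates the risk differences then differ: in step 2 they are 24.0 − 12.3 = 11.7 and 13.6 − 6.55 = 7.1 percentage points. The scale of any claim therefore has to be stated.

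**What to change.** In Reproducibility and Transparency of Research, replace the CART sentence with text to this effect: differential effects by race/ethnicity will be assessed by a treatment-by-race/ethnicity term in a logistic model for month-12 abstinence, as part of the Aim 1 interaction analysis; group-specific risk differences with 95% confidence intervals will be reported; and the analysis is exploratory because power at n = 398 is low. Add that splits on ethnicity in the decision tree describe predicted outcome and are not evidence of a differential treatment effect. Align the description of CART's purpose in the section on matching patients with treatment.

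The cost is a few sentences and one further exploratory model on variables already collected. The interval for the interaction will be wide, and a non-significant result will not show that the effects are equal. The decision tree itself can stay as planned.
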